# Statistics

**8.1. Power calculation**

The primary outcome is reduction in the proportion of service users admitted or detained under a Mental Health Act section at least once, obtained from records. In the pilot trial based in London 26% were compulsorily admitted over 15 months, equivalent to 30% over 18 months. Routine data for inner city wards in Birmingham and Manchester show a very similar proportion, on average. Assuming that a clinically important reduction would be to at least halve the proportion, i.e. a reduction in absolute terms by 15% to 15%, 90% power using a double-sided test with alpha=0.05 would require 174 in each arm. For the ethnic subgroup analysis (see 3.17), where the baseline compulsory admission rate is likely to be higher, an achieved subsample of 91 per arm would give 80% power to detect a difference from 40% to 20% Given the percentages of service users likely to be black at each site (from recent actual MHA use data), 90 are likely to be found with a sample of 270 per arm, and the minimum achieved would be about 80 with a slight reduction in power. Loss to follow-up is likely to be about 15% for the interview data so this sample size (270) would reduce to an effective 229 per arm, which would allow standardised effect sizes of 0.3 for the secondary outcomes to be detectable with 90% power. The total to be recruited would therefore be 540, or 180 per site (which includes 48 who will also have qualitative assessments after 18 month follow-up).

**8.2. Analysis plan**

The principal analysis of effectiveness will compare the primary and secondary outcome measures at 18 months, combined over centres. The proportions admitted to hospital under a section at follow up will be compared between randomisation groups using logistic regression controlling for centre. Other (continuous) outcomes such as therapeutic alliance and engagement with mental health services will be analysed using analysis of covariance controlling for baseline (pre-intervention) measures and centre. Number of admissions will be analysed using Poisson regression, and time to first admission using survival analysis. Bed-days and other very skewed data will be analysed using bootstrapping to obtain confidence intervals and p-values70. Short scales will be analysed using ordered logistic regression. An intention-to-treat analysis will be applied in the first instance (i.e. analysing all available data from service users as randomised). Time trends in measures available at baseline and two time points will be analysed using methods for longitudinal data such as random effects regression. Sensitivity analyses will be performed to assess the influence of loss to follow-up and refusals, including imputation of missing baseline values from the within-centre means; multiple imputation of follow up values (where feasible from other variables) and CACE analyses65. (Full analysis plan is in Appendix 4)

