**Outcome measures**

| **Therapeutic Process** | **Standardised measure** | **Source** | **Time** |
| --- | --- | --- | --- |
| Trust | Mechanic Trust Schedule57 | Focus Groups | FU |
| Recovery Style | Recovery Style Q’re 58,59 | Self-report | B FU |

| **Outcome** | **Standardised measure** | **Source** | **Time** |
| --- | --- | --- | --- |
| MHA use | Routine hospital datasets | Admin. records | B FU |
| Costs | Adult Service Use Schedule | Interview | B FU |
| Perceived coercion | Admission Experience Inventory (Community)48 | Self report | B FU |
| Engagement with care | Engagement and Acceptance Scale 49 and **Service Engagement Scale 60** | Staff self report | B FU |
| Therapeutic relationship | Working Alliance Inventory50 | Self-report | B FU |

B=Baseline, FU Follow-up at 18 months post baseline

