**Statistical Methods**

The principal analysis will compare the primary and secondary outcome measures at 18 months, combined over centres. The proportions admitted to hospital under a section at follow up will be compared between randomisation groups using logistic regression controlling for centre and ethnic group.

Other (continuous) outcomes such as therapeutic alliance and engagement with mental health services will be analysed using analysis of covariance controlling for baseline (pre-intervention) measures, ethnic group and centre. Short scales will be analysed using ordered logistic regression, otherwise linear regression. Bed-days and other very skewed data will be analysed using bootstrapping to obtain confidence intervals and p-values.

Number of admissions (informal and under MHA) will be analysed using Poisson regression, and time to first admission using survival analysis

SPSS version 12 and Stata version 10 will be used for the analyses.

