**Planned Subgroup Analyses**

- Ethnic group (Whites, the combined Black subgroup, which consists of black Caribbeans and black Africans, and others).

The study is not specifically powered to detect interactions between ethnic group and treatment arm. However the black group is considered to be of interest in its own right and therefore a parallel analysis will be applied to this subgroup. The purpose would not be to identify differences compared to the white group but to separately establish the effectiveness of the intervention for black clients.

- Facilitators: the scope for analysing their individual effect will be limited (although see above under fidelity: the fidelity score for particular facilitator/user meetings will be included in further exploratory analyses of intervention effects and also to compare clinical facilitators with their nonclinical backups.
- Care coordinators: variation contributed by care coordinators will be taken account of by including them as random effects in regression models, in which the effect of their characteristics will also be assessed.

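### Section 8.2 and the appended analysis plan give different covariates for the same primary logistic model and for the ANCOVAs, and nothing says which governs

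*Protocol*

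**What the plan says.** **Primary outcome.** In section 8.2 the proportions detained are compared "using logistic regression controlling for centre. Other (continuous) outcomes such as therapeutic alliance" follow with their own method. In Appendix 5, Statistical Methods, they "will be compared between randomisation groups using logistic regression controlling for centre and ethnic group".

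**Continuous outcomes.** Section 8.2 specifies "analysis of covariance controlling for baseline (pre-intervention) measures and centre". Appendix 5 specifies "analysis of covariance controlling for baseline (pre-intervention) measures, ethnic group and centre".

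**Care co-ordinators.** Appendix 5, under Planned Subgroup Analyses, says that "variation contributed by care coordinators will be taken account of by including them as random effects in regression models". It does not say which regression models.

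**Baseline MHA use.** The outcome table in section 7 has the row "MHA use | Routine hospital datasets | Admin. records | B FU", that is, baseline and follow-up. The measures table in Appendix 5 agrees. No statement of the primary model includes the baseline value.

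**Status of the two texts.** Section 8.2 refers to the appendix as the full plan, but the appendix is marked as a second draft dated August 2008. Section 8.2 and the contents list number it Appendix 4. In the body it is headed Appendix 5, and Appendix 4 is the blinding document.

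**The concern.** The trial is decided by one two-sided test at 0.05, and Appendix 5 makes no multiplicity adjustment. That presumes a single primary model. Here there are two, and an analyst could defend either from the protocol after seeing the results.

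Ethnic group is not an idle covariate in this trial. Randomisation is stratified by centre only, so ethnic balance between arms is left to chance. Section 8.1 expects the detention rate to be higher in Black participants. Including or omitting the term can therefore move the estimate and the p-value.

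**Working it through.** **1. The plan's own figure.** Inputs from section 8.1: 30% versus 15%, 90% power, two-sided alpha 0.05.

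n = [1.96·√(2·0.225·0.775) + 1.2816·√(0.30·0.70 + 0.15·0.85)]² / 0.15² = (1.1575 + 0.7445)² / 0.0225 ≈ 160.8, so 161 per arm.

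With continuity correction: (160.8/4)·[1 + √(1 + 4/(160.8·0.15))]² ≈ 173.9, so 174 per arm, as stated. The subgroup figure of 91 per arm (40% versus 20%, 80% power) also reproduces with the correction. The point does not rest on a wrong sample size.

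**2. The statements side by side.**

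| Analysis | Section 8.2 | Appendix 5 |
|---|---|---|
| Primary logistic model | centre | centre, ethnic group |
| ANCOVA | baseline, centre | baseline, ethnic group, centre |
| Care co-ordinator random effects | not mentioned | in unspecified regression models, under subgroup analyses |
| Baseline MHA use in primary model | no | no |

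**3. How prognostic the protocol expects ethnic group to be.** Section 8.1 gives 30% overall, 40% in the Black subgroup, and about 90 Black participants of 270 per arm. The implied rate in the others is (270·0.30 − 90·0.40)/180 = 45/180 = 25%. The odds ratio for ethnic group is (0.40/0.60)/(0.25/0.75) = 2.0.

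**4. What each model estimates.** Without ethnic group: (0.15/0.85)/(0.30/0.70) = 0.412. With it, the conditional odds ratio that keeps the intervention arm at 15% overall is 0.404. Check: the odds become 0.333·0.404 = 0.135 (11.9%) and 0.667·0.404 = 0.269 (21.2%), and ⅔·11.9% + ⅓·21.2% ≈ 15.0%. Wald power at 270 per arm is 98.4% without and 98.6% with ethnic group.

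**5. How often the models disagree on significance.** Simulation: 540 participants, one third Black, control rates 40% and 25%, common risk ratio, 4,000 to 6,000 trials per scenario. The ranges cover repeated runs; the last row is from one run.

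| Risk ratio | Trials with discordant significance |
|---|---|
| 1 (no effect) | 1.5% to 1.6% |
| 0.75 | 4.2% to 4.6% |
| 0.65 | 2.8% to 3.1% |
| 0.5 (design) | 0.4% |

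**6. Type I error if the favourable model is picked.** P(either significant) = [P(A) + P(B) + P(discordant)]/2. In one run this is (5.0 + 5.2 + 1.6)/2 = 5.9%. In another, single-model rates of 5.4% and 5.5% gave 6.2%. The excess over either model alone is 0.7 to 0.9 points.

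**7. Care co-ordinator random intercept.** The documents give no intraclass correlation. For assumed values of 0.02, 0.05, 0.10 and 0.20, the conditional odds ratio matching 30% versus 15% is 0.408, 0.401, 0.390 and 0.366.

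**8. Adding baseline MHA detention.** Its prevalence and prognostic strength are assumptions. At 30% versus 19% with prevalence 40% to 50%, simulated power rises by about 0.5, 1 and 3 to 4 points for a covariate odds ratio of 2, 3 and 5 (at prevalence 40%: 84.7% to 85.9% for 3, and 85.9% to 89.1% for 5). At the design effect with 270 per arm and 50% prevalence, power goes from 98.4% to 98.6%, 98.9% and 99.1% for odds ratios of 2, 4 and 6.

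**The case against.** The best defence is that section 8.2 is a summary and the appendix is the full plan, so the appendix governs. The appendix also leaves other items open, so finalisation was plainly expected. This softens the conflict but does not remove it. No text gives precedence, the fuller text is a draft, and section 8.2 is a complete statement that differs in substance.

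It is also fair to say that the effect is small: the odds ratios are 0.412 and 0.404, discordance at the design effect is 0.4%, and the type I excess is below one point. That stands.

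Two stronger readings are tempting and should be resisted:

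- A reader might infer that there are three conflicting primary models. The care co-ordinator sentence sits among the subgroup analyses, beside facilitator effects, and the primary-model sentence in the same appendix does not mention it. It is an ambiguity, not a third stated model.
- A reader might infer that leaving out baseline MHA use is an error or biases the result. A randomised comparison controlling for centre is valid without it. The documents give no association between earlier and later detention, so they do not support calling it the strongest predictor. Requiring an admission in the previous two years, and excluding current in-patients and people on compulsory community orders, may narrow its spread.

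**Conclusion.** The contradiction is real. The covariate set differs between section 8.2 and Appendix 5 for the primary model and for the ANCOVAs, and the document does not resolve it. It must be corrected because it concerns the one analysis that decides the trial, not because the numerical effect is large. The discordance figures assume one third Black participants, control rates of 40% and 25% (from section 8.1) and a common risk ratio. The care co-ordinator wording needs clarifying. The omission of baseline MHA use forgoes a small gain in precision, whose size depends on assumptions that the documents cannot confirm.

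**What to change.** Before outcome data are unblinded:

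1. State one identical primary model in section 8.2 and Appendix 5: logistic regression on arm with centre and ethnic group. Ethnic group belongs in it because the protocol expects it to be prognostic and does not stratify on it. Code it as White, Black (Caribbean and African combined) and other, since Appendix 5 lists four categories in the baseline table and three under subgroups.
2. Use the same covariates plus the baseline score in the ANCOVAs.
3. Name the care co-ordinator random-effects model as a sensitivity analysis.
4. Say which text governs, and correct the appendix number in section 8.2.
5. As an optional improvement, add baseline MHA detention (yes/no) to the primary model. Neither measures table gives a look-back window, so one must be stated.

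The cost is a sentence or two in each place and one decision on the look-back window. No new data are needed and the sample size is unaffected.

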**8.3. Health Economic analysis**

The JCP intervention will be costed using recognised micro-costing methods65. Costs will be based on the mid-point of the salary scale of the relevant JCP professionals, including all employer costs (National Insurance and Superannuation contributions) and appropriate overhead costs (capital, administration, managerial etc). Other services will be costed using locally applicable estimates of long-run marginal opportunity costs. Where necessary, these will be supplemented by published national unit costs66. Nationally applicable unit costs will be applied in sensitivity analysis to assess the generalisability of the cost results to the UK as a whole. Productivity losses will be costed using the human capital approach, which involves multiplying days off work due to illness by the individual’s salary level67. A number of commentators have argued that this approach is limited since it tends to overestimate productivity losses by ignoring, for example, the ability to replace workers from the pool of unemployed people. Given these limitations, the impact of varying productivity losses will be explored in sensitivity analysis*.*

The mean costs in the two groups will be compared with confidence intervals for mean differences estimated using bootstrapping. Regression models will be used to adjust for baseline characteristics. Future costs will not be discounted in the main analyses because the single follow-up point will not allow costs that fall within the first 12 months to be separated from those which occur subsequently. However, the potential impact of excluding discounting will be explored in sensitivity analyses. Cost-effectiveness will be explored using the proportion admitted under a section over the 18-month follow-up period. Incremental cost-effectiveness ratios (of the additional costs to the additional effects of the JCP process in comparison to the control group) will be reported71 and cost-effectiveness acceptability curves showing the probability that the JCP is more cost-effective than the control condition will be plotted70. Supplementary evaluation will take the form of a cost-consequences analysis examining total costs in relation to all other secondary outcomes69. SPSS version 12 and Stata version 9 will be used for the analyses.

# Risks

Developing JCPs involves reviewing the service user’s experiences of previous admissions and considering the possibility of future relapses. Some service users can find this stressful, either because they recall distressing experiences or because they develop further insight into the severity of their problems. One potential risk is that the stress of developing a joint crisis plan could be a factor in precipitating further relapse. In the pilot study43 this was observed in 1 of 40 service users, who did not need admission. In the earlier RCT44 the intervention group had fewer admissions and adverse events (self harm or violence), indicating that the overall effect was to reduce rather than increase risk.

A further potential risk is that service users will make statements refusing essential or life saving treatment, or state a preference for inappropriate treatment. This is a risk present in the development of advance directives and crisis cards, although there is no legal obligation on doctors to act on advance consent to treatment. If the service user and the team are unable to agree that a treatment choice is clinically acceptable the user can choose whether a statement to that effect is included on the Joint Crisis Plan, or the plan will be reclassified as a Crisis Card indicating the lack of agreement. This occurred on only 1 occasion in the pilot study. If an advance refusal of treatment stated on a JCP is considered by staff to put a service user at risk during a crisis the refusal could be over-ruled by the use of the Mental Health Act 1983.

# Data Handling And Record Keeping

All data will be anonymised and entered on a secure database developed and maintained by the Clinical Trials unit at the Institute of Psychiatry. The only documentation which will contain identifying material are the participant contact details, participant invitation letters (containing name and address), consent form (containing name). All paper forms of this data will be stored in locked filing cabinets at each of the sites and transferred to the Study Coordinating Centre at the end of the study. Only the research team will have access to these filing cabinets. All other data will be identified by a Subject Identification Number only. A file linking the Subject Identification number and personal data will be password protected and stored on a secure server at the Study Coordinating Centre. Only the research team will have access to this data.

All members of the study team will receive Good Clinical Practice training and specific instruction regarding

maintaining confidentiality of data.

# Data Access

This study will generate qualitative data comprising interview transcripts and associated analyses, and quantitative data from questionnaires. Exclusive use for primary research by the research team is envisaged for no more than 2 years following the study, to meet our dissemination goals. Both the quantitative and qualitative data will be shared in anonymised form. Secondary re-analysis of data are anticipated as well as contribution to larger datasets of routinely collected outcome data. Archiving and curating (including data sharing agreements and management of access rights) will be undertaken within the framework used by King’s College London, with due attention to issues of ethical (including consent and confidentiality aspects), legal and institutional regulatory permissions. Intellectual property rights for the data will be retained by the lead applicant and King’s College London.

# Publication

The results of the research will be targeted for publication in peer-reviewed journals of general and special interest. Publication protocol is attached in Appendix 4. At the conclusion of the trial, participants will be sent a report outlining the major findings of the study.

# Appendix 3 – Recruitment Plan

# Appendix 4 – Risks to blinding

Blindness to patient treatment allocation is an important methodological aim of this trial. The following procedures will be used to ensure that blindness is maintained throughout the trial.

**Randomisation**

1. It is the responsibility of the Research Workers to collect all baseline data from participants and electronic patient systems ***before*** alerting the Coordinator that the participant is ready to be randomised.
2. Research Workers will not be involved in the randomisation of subjects, other than alerting the Coordinator that a participant is ready to be randomised. After fully completing the baseline assessment interview, Research Workers will inform [name] via the dedicated form in the data entry database that the participant is ready to be randomised. SF will then access the online randomisation service hosted by the IOP CTU and enter in the participants details. The Research Workers will receive an email alerting them to the fact that their participant has been randomised. At this point, the Research Worker will then enter that they have received confirmation of randomisation in the data entry database. The baseline data for this individual will then be blocked.
3. After the randomisation confirmation has been received by the Research Worker and they have entered this into the data entry database, Research Workers should not look at the participants clinical notes again.
4. The JCP facilitator at each site will receive an email informing them that a participant has been randomised and to which intervention arm. It is the responsibility of the facilitator at each site to ensure that the Research Workers do not see this correspondence.
5. The facilitator at each site will then inform both the control and intervention groups of the allocation. It is the responsibility of the facilitator to ensure that the Research Workers do not see this correspondence.
6. When discussing the allocation with the participant, the facilitator will give the participant the SF’s or local Trial administrator’s number in case he or she wishes to discuss the allocation further at a later date.
7. Facilitator to file randomisation notification emails and other identified information regarding intervention arm, in locked filing cabinet separate to Research Worker files

**Intervention**

Facilitators and local site lead PI have a responsibility to ensure that Research Workers do not discover which participants receive the intervention by:

1. Ensuring that Research Workers are using separate offices, phone numbers, file storage to the facilitators.
2. Ensuring that team research meetings do not involve discussion of the participants, even in casual conversation. Team meetings may be conducted with a portion that is not attended by the research workers in which any specific participants can be discussed.
3. Facilitators should remind the participant at the JCP and content checking meetings, and at any subsequent contact with the participant that the Research Worker should not know the group allocation. Family members and clinical staff should also be reminded that blindness must be maintained.
4. If possible, Research Workers should inform the facilitators of their upcoming assessments (e.g. in meeting minutes or passing the appointment information to the administrator) so that facilitators can avoid being in the same location at the same time for the JCP meetings and content checks.
5. Where possible and safe, Research Workers should conduct assessments at participants homes or places other than the CMHT building.

